**Figure 2 F2:**
[figure not shown]
**Structure of the MDPS Group Program.** IS: Individual session.S1-S5: group sessions.T1, T2, T3: anthropometric and laboratory tests.

The theoretical framework of this intervention is based on the Health Action Process Approach (HAPA) model and self-regulation theory
[18-20]. Several other theories, strategies and constructs are incorporated into the design of the intervention. These include the social learning theory, the trans-theoretical theory of stages of change
[21,22], empowerment-oriented counseling
[23-25], goal-setting approach
[26,27], self-efficacy and self-evaluation
[18,28].

The group sessions follow the structure of the HAPA model. Each session is structured with a major emphasis on creating an interactive and socially-supportive atmosphere. In these sessions the facilitator enables goal setting, moderates the discussion and feedback, and strengthens the role of the group as a source of social support. In addition, individual feedback is provided to participants from anthropometric and laboratory measurements at the second clinical testing session (which follows the fourth group session - approximately three months after the commencement of the intervention). This individual feedback is used to evaluate the impact of the intervention and to sustain participants’ motivation in their lifestyle changes.

### Outcome assessments

#### Primary outcomes

The primary outcomes under investigation are changes in diabetes and CVD risk as determined by changes in weight, waist circumference, fasting plasma and two-hour glucose, blood pressure and lipids. These are determined through anthropometric and laboratory measurements (performed as detailed below) at baseline, following the fourth group session (approximately three months after the commencement of the intervention) and 12 months after commencement of the intervention. The reduction in diabetes risk is calculated from the reduction in weight and waist circumference
[12] and the reduction in cardiovascular risk from changes to the Framingham risk score, which incorporates the changes in the individual risk factors.

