### The Melbourne diabetes prevention study (MDPS)

The Melbourne Diabetes Prevention Study (MDPS) is a research project set up to study in detail a cohort of individuals undertaking the Life! program in order to evaluate the effectiveness of a large-scale prevention program and, importantly, the cost-effectiveness. The focus of the present study is a specific modification of the program developed in 2011. The program to be evaluated consists of an individual session and five group sessions (‘1+5 model’) as presented further below.

The working hypotheses of the MDPS are that (1) the MDPS program results in statistically and clinically significant changes (relative to usual care) in clinical, behavioral, and patient relevant outcomes, particularly changes in weight and waist circumference, that reduce the risk of progression to T2DM; and (2) the diabetes prevention program provided in this study is both ‘cost-effective’ (relative to usual care using a yardstick of $50,000 per quality adjusted life year (QALY)) and performs well in the second stage filter implementation analysis (the protocol for the economic appraisal will be presented separately).

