### Anthropometric measurements

Height is measured at baseline and confirmed at subsequent testing using a portable height stadiometer (Charder). Participants are asked to remove their shoes and any hair ornaments. Height is recorded to the resolution of the height rule (1 mm).

Weight is measured with a weight scale (Charder MS3200) placed on a hard surface. The scale is tested in order to check that it gives a zero value. Participants are asked to remove their heavy outer garments and shoes, empty their pockets and remove heavy belts and items. The participant stands in the center of the platform, with weight evenly distributed between both feet. Weight is recorded to the resolution of the scale (0.1 kg).

The waist circumference is measured with a measuring tape (Seca203). The length of the tape is checked every month against the height rule. If the measuring tape is stretched it is replaced. Waist circumference is measured at a level midway between the lower rib margin and the iliac crest with a tape around the body in a horizontal position. Participants are asked to remove their clothes, except for light underwear. Measurements are recorded twice according to the resolution of the tape (1 mm) and the mean is used for data analysis.

Hip circumference is measured as the maximal circumference over the buttocks. The measurement procedure is the same as for the waist measurement with the exception of the tape position.

Blood pressure is measured with an electronic sphygmomanometer (Omron HEM-907). Blood pressure will be measured in the sitting position after at least five minutes rest. The measurement is taken from the bare right upper arm. The arm should be resting on the desk so that the antecubital fossa is level with the heart and the palm of the hand is facing up. The cuff should be placed on the right arm and its bottom edge should be 2 to 3 cm above the antecubital fossa. The top edge of the cuff should not be restricted by clothing. Two measurements are taken one minute apart and the mean is used for data analysis. If the second measurement differs by more than 10 mmHg systolic or 6 mmHg diastolic, a third measurement is taken one minute later. The mean of the closest two systolic and diastolic measurements is used for analysis.

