### Sample size and power calculation

For the estimation of sample size for two groups, with a two-sided 5% significance level and 80% power, the total number required will be 598 (299 in each arm). The sample size calculation was based on the observed mean change in diastolic blood pressure, a CVD risk factor, in the GGT-DPP and powered to detect an effect size of at least 0.23. To allow for an estimated attrition of up to 25% (estimate based on the GGT DPP), we require a total sample of 796 (398 in each arm). This sample size will provide sufficient power for other CVD risk factors, such as total and high-density lipoprotein (HDL)-cholesterol, as well as diabetes risk factors including fasting plasma glucose, weight, and waist circumference, as these are all expected to have larger effect sizes.

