### Data analysis

Analyses will be performed using Stata version 12 or later, and the ‘intention-to-treat’ principle will be adhered to. Baseline characteristics will be compared between intervention and control groups using chi-square tests, independent t-tests, and the Wilcoxon rank-sum test as appropriate. Primary and secondary outcomes (as described above) will be evaluated using mixed models, treating ‘group’ as a between-subject factor and ‘time’ as a within-subject factor. Two-sided tests will be used, with a level of *P* <0.05 determining statistical significance.

A separate and parallel economic evaluation protocol will be described elsewhere.

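### Several unranked primary outcomes share one two-sided 5% level, so a claim of effectiveness resting on any one of them does not carry a 5% error rate

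*Protocol article*

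**What the plan says.** All references are to the protocol article.

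- **Primary outcomes.** The section uses the plural. It presents the primaries as changes in diabetes and cardiovascular risk, determined through "changes in weight, waist circumference, fasting plasma and two-hour glucose, blood pressure and lipids". It then derives diabetes risk from weight and waist, and "the reduction in cardiovascular risk from changes to the Framingham risk score". No item is placed first.
- **Data analysis.** "Primary and secondary outcomes (as described above) will be evaluated using mixed models", and tests are two-sided "with a level of *P* <0.05 determining statistical significance". The section gives no order, no division of the level and no criterion for overall success.
- **The Melbourne diabetes prevention study (MDPS).** The first hypothesis covers clinical, behavioural and patient-relevant outcomes, "particularly changes in weight and waist circumference, that reduce the risk of progression to T2DM".
- **Sample size and power calculation.** The calculation was "based on the observed mean change in diastolic blood pressure, a CVD risk factor, in the GGT-DPP", with a two-sided 5% level, 80% power and effect size 0.23. It gives 299 per arm, or 398 per arm after 25% attrition. The section then states that power suffices for total and HDL cholesterol, fasting glucose, weight and waist, because larger effects are expected for them.

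**The concern.** Three sections point to three different leading outcomes: everything in the list, weight and waist, or diastolic pressure. With one significance level for all of them, an analyst could present any of these as the main result without departing from the text. The nominal 5% describes each single test. It does not describe the claim that the programme works when that claim may rest on whichever primary turned out significant.

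The Discussion says the results, with the economic evaluation, are to inform policy and guidelines on diabetes prevention. A lone significant lipid or blood pressure result could be read as confirmation, with a false-positive risk well above 5%. The sample size makes no allowance for more than one test.

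**Working it through.** **1. The plan's own figure.** Inputs from the sample size section: effect size 0.23, two-sided 5%, 80% power.

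n per arm = 2(1.960 + 0.842)² / 0.23² = 297 (298 with the t distribution), against 299 stated. At 299 per arm, power is 80.3%. Attrition: 299 / 0.75 = 398.7, against 398 stated. The figure is reproduced to within two participants, and only for one uncorrected 5% test.

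**2. How many primaries?** The article gives no count. The possible readings are:

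- Two: the diabetes-risk and cardiovascular-risk constructs.
- Six: weight, waist, fasting glucose, two-hour glucose, blood pressure, lipids.
- Eight: blood pressure split in two (Anthropometric measurements: "The mean of the closest two systolic and diastolic measurements is used for analysis") and lipids split into at least total and HDL cholesterol, which the sample size section names separately.

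The three-month visit adds no between-arm test, because controls are not measured then.

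**3. Chance of at least one P<0.05 when no outcome has a true effect.** For independent tests this is 1 − 0.95^k:

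- k = 2: 1 − 0.9025 = 9.75%
- k = 6: 1 − 0.7351 = 26.5%
- k = 8: 1 − 0.6634 = 33.7%

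The document gives no correlations between outcomes, so a common correlation r is assumed and varied. Results are from simulated normal test statistics (400,000 draws), counting draws in which the largest absolute value exceeds 1.96:

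| k | r = 0 | r = 0.3 | r = 0.5 | r = 0.7 | r = 0.8 |
|---|---|---|---|---|---|
| 2 | 9.8% | 9.5% | 9.0% | 8.3% | 7.8% |
| 6 | 26.5% | 24.1% | 20.8% | 16.4% | 14.0% |
| 8 | 33.7% | 30.0% | 25.1% | 19.0% | 15.7% |

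A block pattern for k = 8 was also tried: weight with waist 0.8, the glucose pair 0.4, systolic with diastolic 0.7, the lipid pair 0.2, all others 0 to 0.2. It gives 29% to 31%. These correlations are assumptions too.

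**4. Power under a correction, at 299 evaluable per arm.** The standard error of the standardised difference is √(2/299) = 0.0818, so 0.23 / 0.0818 = 2.812.

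- Level 0.05: 2.812 − 1.960 = 0.852, power 80.3%.
- Level 0.025 (first Holm step for two outcomes): 2.812 − 2.241 = 0.571, power 71.6%.
- Effect needed for 80% power at 0.025: (2.241 + 0.842) × 0.0818 = 0.252.
- Level 0.05/8 = 0.00625 (Bonferroni over eight): power 53.1%. Holding 80% would need 484 evaluable per arm, and 484 / 0.75 gives 646 per arm recruited.

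**The case against.** The strongest reply is grammatical. The sentence in the Primary outcomes section makes diabetes risk and cardiovascular risk the outcomes, and the measurements are how they are determined. That gives two primaries and an error of at most about 10%. The reading is possible and sets the lower end of the range. It fits the rest of the text poorly: diabetes risk is calculated from weight and waist only, so two-hour glucose has no clear role. The sample size section also discusses power for individual measures and for neither score.

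A second reply is that multiplicity is often handled in a statistical analysis plan, which is not shown. Silence alone would be no finding. The article, however, goes further: it lists unranked primaries, fixes one level for all of them, and sizes the trial on a single test of an outcome that its hypothesis does not emphasise.

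Three stronger readings are tempting, and the document does not support them:

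- That there are at least eight co-equal primaries. Eight is an inference from splitting blood pressure and lipids.
- That the error reaches 40% (1 − 0.95^10). This treats the two scores as independent of the measures from which they are calculated.
- That the plan's rule allows a claim on any single outcome. No success rule is stated; nothing stated prevents such a claim. The hypothesis also asks for clinical as well as statistical significance, which an isolated lipid result might not meet.

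**Conclusion.** The point holds. As written, the plan does not secure a 5% error rate for a claim of effectiveness based on any one primary outcome. The error is about 10% if only the two risk constructs count, and about 16% to 34% if eight components count, depending on an assumed common correlation from 0.8 down to 0. These figures apply when no outcome has a true effect. They are not figures from the document, and both the count and the correlations behind them are assumptions. On every reading examined the error exceeds 5%. The defect is one of specification, and wording can remove it at a modest cost in power.

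**What to change.** Make the change before any between-arm outcome data are examined, and record its date. The trial is open, recruitment began in September 2011, and 266 participants had been randomised by 15 November 2012. Some 12-month measurements may therefore already exist.

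- **Primary outcomes:** name the 12-month between-arm differences in weight and in waist circumference, which the hypotheses already single out. Test the pair with Holm at a familywise 5%.
- **Other outcomes:** test glucose, blood pressure, lipids and the calculated risk scores only after primary success, in a fixed sequence or with Holm. Otherwise, report them with intervals and no confirmatory claim. State what counts as success for this step: ordinary Holm releases the full 5% only when both primaries are rejected, so opening the next family after one needs an explicit share of the level.
- **Data analysis:** replace the single P<0.05 sentence to match.
- **Sample size and power calculation:** restate it for weight and waist.

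Cost: at 299 evaluable per arm, power at effect size 0.23 falls from about 80% to 72% at the first Holm step, and 80% power then needs an effect of about 0.25. The article expects larger effects for weight and waist but gives no figures, so the restated calculation should supply them. The cardiovascular measures also leave the primary set, although the article treats cardiovascular risk as an aim. If the sponsor finds that unacceptable, a single named primary or a fixed sequence keeps the first test at 5%.

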#### Secondary outcomes

Changes in psychosocial and quality of life measurements (performed as detailed below) are the secondary outcomes.

There is also an economic assessment of the program (separate protocol) by evaluating: whether it is ‘value for money’ through Cost Utility Analysis (CUA), evaluating technical efficiency issues through Cost Effectiveness Analysis (CEA) and by assessing a broader range of factors to supplement the technical analysis, based on second stage filter implementation analysis pioneered in Assessing Cost-Effectiveness (ACE) projects
[29]. The final aim is to evaluate the ‘usual care’ of individuals at high risk of progression to T2DM.

### Anthropometric measurements and laboratory testing

Study nurses are specifically trained to undertake standardized anthropometric measurements including height, weight, waist and hip circumferences, and blood pressure. These measurements and the laboratory procedures follow the international recommendations: the World Health Organization’s Multinational Monitoring of Trends and Determinants in Cardiovascular Disease (MONICA) Protocol
[30] and the latest recommendations of the European Health Risk Monitoring protocol
[31]. All measurements are recorded on the Clinical Test Form and are performed at baseline, following the fourth group session (approximately three months after the commencement of the intervention) and 12 months after commencement of the intervention for the intervention group and only at baseline and 12 months for the control group.

### Anthropometric measurements

Height is measured at baseline and confirmed at subsequent testing using a portable height stadiometer (Charder). Participants are asked to remove their shoes and any hair ornaments. Height is recorded to the resolution of the height rule (1 mm).

Weight is measured with a weight scale (Charder MS3200) placed on a hard surface. The scale is tested in order to check that it gives a zero value. Participants are asked to remove their heavy outer garments and shoes, empty their pockets and remove heavy belts and items. The participant stands in the center of the platform, with weight evenly distributed between both feet. Weight is recorded to the resolution of the scale (0.1 kg).

The waist circumference is measured with a measuring tape (Seca203). The length of the tape is checked every month against the height rule. If the measuring tape is stretched it is replaced. Waist circumference is measured at a level midway between the lower rib margin and the iliac crest with a tape around the body in a horizontal position. Participants are asked to remove their clothes, except for light underwear. Measurements are recorded twice according to the resolution of the tape (1 mm) and the mean is used for data analysis.

Hip circumference is measured as the maximal circumference over the buttocks. The measurement procedure is the same as for the waist measurement with the exception of the tape position.

Blood pressure is measured with an electronic sphygmomanometer (Omron HEM-907). Blood pressure will be measured in the sitting position after at least five minutes rest. The measurement is taken from the bare right upper arm. The arm should be resting on the desk so that the antecubital fossa is level with the heart and the palm of the hand is facing up. The cuff should be placed on the right arm and its bottom edge should be 2 to 3 cm above the antecubital fossa. The top edge of the cuff should not be restricted by clothing. Two measurements are taken one minute apart and the mean is used for data analysis. If the second measurement differs by more than 10 mmHg systolic or 6 mmHg diastolic, a third measurement is taken one minute later. The mean of the closest two systolic and diastolic measurements is used for analysis.

### Laboratory measurements

Participants are asked to fast from 10 pm the night prior to their appointment and samples are drawn for fasting plasma glucose (FPG), HbA1c and lipid profile at baseline, following the fourth group session (approximately three months after the commencement of the intervention) and 12 months after commencement of the intervention and only at baseline and twelve months for the control group. Compliance with fasting is recorded before each clinical test by asking participants the duration of their fasting period. A two-hour OGTT follows in which the participant ingests a 75 g glucose solution. Two hours after this a further blood sample for glucose is taken. The time of the glucose ingestion and second blood withdrawal are recorded. The OGTT is performed at baseline and 12 months for both intervention and control arms.

The baseline results from the FPG and two-hour OGTT determine the final eligibility. If diabetes is diagnosed (FPG greater than or equal to 7 mmol/L and/or two-hour glucose greater than or equal to 11.1 mmol/L), the individual will be referred to their GP and will not be eligible to enter the study.

All patients who complete the clinical testing receive a letter documenting their results, with standardized feedback. A copy is also sent to their nominated GP. If diabetes is diagnosed, an individual covering letter is sent to the participant referring them back to their GP for suitable treatment.

Additional blood from consenting participants will be drawn and bio-banked at −70°C (ULT REVCO 1786) for further possible biochemical analysis.

### Psychosocial and quality of life measurements

Self-reported questionnaires are given to participants at baseline, following the fourth group session (approximately three months after the commencement of the intervention) and 12 months after commencement of the intervention. Health status questions include demographics, smoking status, history of diabetes, myocardial infarction, cancer and mental disorders. Self-regulation
[32], self-efficacy specified for diet and physical activity
[18,19,33,34], risk perception for diabetes, lifestyle planning, social support
[35], and quality of life (AQoL8D)
[36] are assessed. The Hospital Anxiety and Depression Scale (HADS)
[37], the health related hardiness
[38] and a physical activity assessment (Active Australia)
[39] are also part of this questionnaire. Food Frequency Questionnaires (FFQ)
[40] are completed at baseline and 12 months. Participants are also asked to complete a questionnaire related to the evaluation of the MDPS intervention at the 12 month clinical test.

If a participant scores 11 or more on the HADS tool for anxiety and/or depression at any of the testing sessions, an individual covering letter is sent to the participant referring them back to their GP for suitable treatment.

### Sample size and power calculation

For the estimation of sample size for two groups, with a two-sided 5% significance level and 80% power, the total number required will be 598 (299 in each arm). The sample size calculation was based on the observed mean change in diastolic blood pressure, a CVD risk factor, in the GGT-DPP and powered to detect an effect size of at least 0.23. To allow for an estimated attrition of up to 25% (estimate based on the GGT DPP), we require a total sample of 796 (398 in each arm). This sample size will provide sufficient power for other CVD risk factors, such as total and high-density lipoprotein (HDL)-cholesterol, as well as diabetes risk factors including fasting plasma glucose, weight, and waist circumference, as these are all expected to have larger effect sizes.

### Randomization

Randomization to either the intervention or usual care arm is made after confirmation of the eligibility of the patient, and after exclusion of T2DM, based on the baseline clinical test results (both FPG <7 mmol/L and OGTT two-hour glucose <11.1 mmol/L). Randomization is generated by a random number table and participant instructions are placed in individual sealed, opaque envelopes. The Project Coordinator selects the next sequential envelope to be attributed to a new participant. A covering letter is sent to participants indicating which group (Intervention or Control) they are allocated to, and what the subsequent processes are for participating in the study.

### Data management

Data are entered on two separate password protected databases: the ‘participant’ database and the ‘intervention’ database. The ‘participant’ database contains data on participants who have been registered in the trial along with their personal details, recruitment method, baseline testing date, allocations, and recall date for testing. This database is hosted on a secure, virtual server and is accessible only by the Project Coordinator, Study Nurse, Facilitator, administrative staff and Senior Program Manager. The second database, the ‘intervention’ database, contains de-identified data including blood test results, questionnaires, and anthropometrics. Data collected from participants at each testing session (baseline, following the fourth group session (approximately three months after the commencement of the intervention) and 12 months after commencement of the intervention) are checked for accuracy and completeness through routine data cleaning and management procedures.

The establishment of two databases allows management of the trial without violation of privacy or confidentiality of participant data and the integrity of allocation concealment. Only the Project Coordinator and specified members of the Study Team have access to identifiable data on a predetermined ‘need-to-know’ basis. The ‘participant’ database supports the regular generation of reports on those participants due for clinical testing, or completing an intervention.

